## Abstract

**Background:**

The frequency of heart failure (HF) in Tunisia is on the rise and has now become a public health concern. This is mainly due to an aging Tunisian population (Tunisia has one of the oldest populations in Africa as well as the highest life expectancy in the continent) and an increase in coronary artery disease and hypertension. However, no extensive data are available on demographic characteristics, prognosis, and quality of care of patients with HF in Tunisia (nor in North Africa).

**Objective:**

The aim of this study was to analyze, follow, and evaluate patients with HF in a large nation-wide multicenter trial.

**Methods:**

A total of 1700 patients with HF diagnosed by the investigator will be included in the National Tunisian Registry of Heart Failure study (NATURE-HF). Patients must visit the cardiology clinic 1, 3, and 12 months after study inclusion. This follow-up is provided by the investigator. All data are collected via the DACIMA Clinical Suite web interface.

**Results:**

At the end of the study, we will note the occurrence of cardiovascular death (sudden death, coronary artery disease, refractory HF, stroke), death from any cause (cardiovascular and noncardiovascular), and the occurrence of a rehospitalization episode for an HF relapse during the follow-up period. Based on these data, we will evaluate the demographic characteristics of the study patients, the characteristics of pathological antecedents, and symptomatic and clinical features of HF. In addition, we will report the paraclinical examination findings such as the laboratory standard parameters and brain natriuretic peptides, electrocardiogram or 24-hour Holter monitoring, echocardiography, and coronarography. We will also provide a description of the therapeutic environment and therapeutic changes that occur during the 1-year follow-up of patients, adverse events following medical treatment and intervention during the 3- and 12-month follow-up, the evaluation of left ventricular ejection fraction during the 3- and 12-month follow-up, the overall rate of rehospitalization over the 1-year follow-up for an HF relapse, and the rate of rehospitalization during the first 3 months after inclusion into the study.

**Conclusions:**

The NATURE-HF study will fill a significant gap in the dynamic landscape of HF care and research. It will provide unique and necessary data on the management and outcomes of patients with HF. This study will yield the largest contemporary longitudinal cohort of patients with HF in Tunisia.

**Trial Registration:**

ClinicalTrials.gov NCT03262675; https://clinicaltrials.gov/ct2/show/NCT03262675

**International Registered Report Identifier (IRRID):**

DERR1-10.2196/12262

## Introduction

### Background

Heart failure (HF) has experienced epidemic growth and has become frequent worldwide. The prevalence of HF among the adult population in developed countries is 1%-2%; however, this rate rises to 10% or more among people aged over 70 [1]. According to recently published data, nearly 26 million people worldwide are living with HF; in particular, in Europe, this number is estimated to be 15 million [1,2]. The global health care cost related to HF is around US $108 billion/year [3]. Despite the development of therapeutic approaches, HF continues to account for a high mortality in up to 50% of patients within 5 years after diagnosis [4]; in particular, one-quarter of patients die within 1 year of diagnosis [5]. Sudden death is the most common cardiovascular cause of death (45%) [6,7].

The frequency of HF in Tunisia is on the rise and has now become a public health concern. This is mainly attributed to an aging Tunisian population (Tunisia has one of the oldest populations in Africa as well as the highest life expectancy in the continent) and an increase in coronary heart disease and hypertension. However, no extensive data are available on demographic characteristics, prognosis, and quality of care of patients with HF in Tunisia (nor in North Africa). Furthermore, the data pertaining to European and American populations cannot be extrapolated to the Tunisian population because of differences in demographics, diagnostic algorithm employed, and therapeutic strategies applied for patients with HF. Therefore, a multicenter observational study focusing on the demographic, prognostic, and therapeutic features of HF in Tunisia is essential. Data from such a study will help us to assimilate our practices, and then to harmonize them in order to optimize the management of patients and to assess the morbidity and mortality of HF as well as the degree of adherence of practitioners to international recommendations in the treatment of this pathology.

### Registry Objectives

The National Tunisian Registry of Heart Failure (NATURE-HF) describes the epidemiological profile of acute and chronic HF cases in Tunisia to evaluate their mobi-mortality over 1 year of follow-up. The morbidity of HF is defined as rehospitalization within 1 year of cardiac failure or flare-up occurring after inclusion of the patient, whereas mortality is defined as occurrence of cardiovascular death (sudden death, sudden cardiac arrest, refractory HF, stroke) or death from any cause (cardiovascular and noncardiovascular).

Several secondary endpoints are defined, including evaluation of (1) cardiovascular death over 1 year of follow-up, (2) all causes of death on a 1-year follow-up, (3) re-admission rate for cardiac insufficiency, (4) adherence of physicians to the European recommendations on medical and interventional therapies, (5) impact of HF on patient’s health, and (6) determination of the predictors of cardiovascular mortality.

## Methods

### Study Design and Patient Enrollment

This is a national, observational, longitudinal, multicenter registry study with a follow-up period of 13 months (1 month of inclusion and 12 months of clinical follow-up and exploratory analysis).

We included 1700 patients with HF, outpatients with chronic HF, and those hospitalized for acute HF. The diagnosis of HF is at the discretion of investigators. All included patients should provide written informed consent.

The exclusion criteria were as follows: estimated life expectancy less than 12 months for extracardiac pathology, isolated right HF, pregnancy, end-stage or severe renal insufficiency with creatinine clearance less than 15 mL/minute, undergoing hemodialysis, cardiac surgery scheduled within 3 months, and congenital heart disease.

Any violation of the protocol (eg, included but actually not eligible as per the selection criteria) will be informed to the Steering Committee which will decide on whether or not to exclude the patient concerned.

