### Sample Size and Data Collection

Patients eligible according to aforementioned inclusion criteria will be selected at the cardiology consultation level or during cardiology or emergency hospitalization. As much as 250 cardiologists (from both public and liberal sectors) will participate in patient selection. Patient inclusion will occur consecutively until the end of the inclusion period. Suitable patients will be selected and requested to sign an informed consent form, confirming their agreement to participate in the study. A detailed questionnaire will then be administered to eligible patients and clinical, biological, and exploratory data will be collected.

The inclusion began on October 2, 2017 (duration 1 month). A regular follow-up was done, wherein patients must visit the cardiology clinic 1, 3, and 12 months after inclusion into the study. This follow-up is provided by the investigator.

Given the observational nature of the NATURE-HF study, no specific treatment or intervention is planned for the management of HF. Patients should be cared for according to the usual medical procedures.

All data are collected via the DACIMA Clinical Suite web interface [8]. The platform complies with international standards FDA 21 CFR part 11 (Food and Drug Administration 21 Code of Federal Regulations part 11), HIPPA (Health Insurance Portability and Accountability Act), ICH (International Conference on Harmonisation), MedDRA (Medical Dictionary for Regulatory Activities), Health Canada, and Tunisian regulations.

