### Statistical Analysis

The DACIMA Clinical Suite platform enables the collection of online data and their extraction in SAS or SPSS format. Statistical analysis will be performed with SAS software (University Edition; SAS Institute). The statistical analysis is exploratory, involving the calculation of 95% CI.

The data will be described for the whole analyzed population. Continuous quantitative variables (eg, age, weight, left ventricular ejection fraction, biological parameters) will be described by the number of patients documented, mean, median, SD, and extreme values. Categorical variables will be described by the number and percentage of each category.

The normality of the continuous quantitative variables will be verified with the Shapiro–Wilk test. If the hypothesis of normality is rejected, then a simple transformation will be made on the variable to normalize it. If this transformation succeeds in normalizing the variable, then the analysis will be performed on the transformed variable. Otherwise nonparametric tests will be used or possibly an analysis on the quartiles or quintiles will be performed.

Statistical tests will be bilateral with a statistically significant threshold of 5%. An analysis of variance will be performed for the quantitative variables (parametric test for the variables that follow a normal distribution, and nonparametric test in other cases) and a chi-square test will be realized for the categorical variables. The Yates correction or Fisher exact test will be used if the validity conditions for the chi-square test are not met (theoretical number <5).

The sample size (both power and sample) is estimated by the SPSS 2008 software (IBM). To estimate the number of patients to be included in this study, a range of 95% CI (5% significance threshold) is set as the primary endpoint. The impact of this criterion is estimated at 35%, based on the US registry OPTIMIZE-HF [9], which found a hospital mortality ranging from 2.2% to 4.1%, a global mortality ranging between 6.5% and 9.1%, and an overall incidence of all events evaluated (rehospitalization or death) ranging from 35.3% to 36.6%.

Considering these data, the number of patients to be included in the study would be 1436. However, by predicting a 5% missing data rate and a 10% loss to follow-up, the sample size to be selected will be 1700 patients.

The intermediate analyses will be carried out after formulating the statistical analysis plan.

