### Data Review

The Data Review Committee includes the Coordinators of the Steering Committee of the study as well as the scientific team of DACIMA Consulting. The purpose of the Data Review Committee is to respond to specific queries in data management, and to validate the statistical procedures developed in the final statistical analysis plan. The Data Review Committee will also be responsible for validating subsequent publications.

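### The Steering Committee may exclude already included patients case by case, with no criterion and nothing that separates the decision from knowledge of follow-up outcomes

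*Protocol article*

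**What the plan says.** The rule is in the protocol article, Study Design and Patient Enrollment. Its scope is "Any violation of the protocol (eg, included but actually not eligible as per the selection criteria"), and each such case "will be informed to the Steering Committee which will decide on whether or not to exclude the patient concerned". Ineligibility is given as an example, so the rule covers violations in general.

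The same section lists the exclusion criteria. Most are facts at baseline, such as pregnancy, hemodialysis or congenital heart disease. One is a prognosis: "estimated life expectancy less than 12 months for extracardiac pathology". The section gives the timetable as "1 month of inclusion and 12 months of clinical follow-up and exploratory analysis".

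Sample Size and Data Collection says of the visits at 1, 3 and 12 months: "This follow-up is provided by the investigator". Statistical Analysis states: "The data will be described for the whole analyzed population". It does not say how that population is formed. Data Review adds: "The Data Review Committee includes the Coordinators of the Steering Committee of the study". That committee answers data-management queries and validates the statistical procedures of the final analysis plan.

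**The concern.** The registry exists to estimate morbidity and mortality over one year. There is no comparison arm in which a selection error might cancel, so the estimate depends directly on who stays in the denominator.

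The rule makes removal optional. It ties the choice to no criterion, no cut-off for the data considered, and no masking. Inclusion lasts one month and follow-up twelve, so a violation found after inclusion closes is judged while outcomes accrue or after they are known. The study is observational, the investigator provides follow-up, and intermediate analyses are foreseen.

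The life-expectancy criterion is the most exposed. Once a patient has died of an extracardiac illness, it is easy to conclude that the prognosis at entry was below 12 months. Registry Objectives counts noncardiovascular deaths in mortality, so excluding that patient removes an endpoint event. The wide scope adds a second route. A missed visit could count as a violation, and it may itself follow from death or readmission.

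**Working it through.** **Step 1: the plan's own figures.** Statistical Analysis gives an expected event rate of 35%, 5% significance, 1436 patients before allowances and 1700 after. It does not state the half-width d of the confidence interval.

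- Precision formula: n = 1.96² × p(1 − p) / d². With p = 0.35 and an assumed d = 0.025, n = 1399, within 3% of 1436.
- Half-width implied by 1436: 1.96 × √(0.35 × 0.65 / 1436) = 0.0247, or 2.47 points. With 1700 patients it is 2.27 points.
- Allowance for 5% missing data and 10% loss to follow-up: 1436 / 0.85 = 1690, or 1436 / (0.95 × 0.90) = 1680. Both are close to 1700.

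The sample size is therefore broadly reproduced and is not in question here. It supplies the yardstick of about 2.5 points.

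**Step 2: the effect of selective removal.** Let N = 1700 and p = 0.35. Let f be the ineligible share, so m = fN patients are ineligible. Assume that ineligible patients have the same event rate as the others. Let a be the fraction removed among ineligible patients with an event, and b the fraction removed among those without. The reported rate is

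R = (Np − a·m·p) / (N − a·m·p − b·m·(1 − p)).

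If a = b, then R = p. Uniform handling, whether keeping or removing, causes no shift under this assumption, so any movement comes from selection alone.

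For f = 5%, m = 85, of whom 29.75 are expected to have an event and 55.25 not. All enrolled patients have 595 events.

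- Fully selective, events removed (a = 1, b = 0): (595 − 29.75) / (1700 − 29.75) = 565.25 / 1670.25 = 33.8%.
- Fully selective, event-free removed (a = 0, b = 1): 595 / (1700 − 55.25) = 595 / 1644.75 = 36.2%.
- a = 0.75, b = 0.25: (595 − 22.31) / (1700 − 22.31 − 13.81) = 572.69 / 1663.88 = 34.4%.
- a = 0.25, b = 0.75: (595 − 7.44) / (1700 − 7.44 − 41.44) = 587.56 / 1651.12 = 35.6%.

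The same formula over a range of f:

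| Ineligible (assumed) | 75% v 25%, events favoured for removal | 75% v 25%, event-free favoured | Only events removed | Only event-free removed |
|---|---|---|---|---|
| 1% (17) | 34.9% | 35.1% | 34.8% | 35.2% |
| 5% (85) | 34.4% | 35.6% | 33.8% | 36.2% |
| 10% (170) | 33.8% | 36.2% | 32.6% | 37.4% |

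**Step 3: mortality.** Assume 8% one-year mortality, inside the 6.5% to 9.1% that the article cites for global mortality. That is 136 deaths in 1700. The half-width at n = 1436 is 1.96 × √(0.08 × 0.92 / 1436) = 1.4 points. With 5% ineligible and the same mortality among them, 85 × 0.08 = 6.8 deaths are at issue. Removing only those gives (136 − 6.8) / (1700 − 6.8) = 7.6%, a shift of about 0.4 points. Reclassification after death could go further. If 17 patients who died were relabelled ineligible, the rate would be 119 / 1683 = 7.1%, a shift of 0.9 points. That count is a stress case with no basis in the article.

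**The case against.** The strongest reply is that much of this is missing detail. The article is condensed and refers to an analysis plan that is not shown. Analysis sets, the timing of the review and masking commonly belong there or in a committee charter. That is fair for an undefined analysis population or an unstated review date taken alone. It does not cover the discretion itself, which the article states as a rule.

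Three stronger readings are tempting, and the article does not support them.

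- A reader might infer that the committee decides with outcomes in view. The article does not say what it sees or when. Only its coordinators sit on the Data Review Committee, and nothing says that exclusions are decided there. What can be said is that nothing prevents it.
- A reader might assume that the bias runs downward and is permanent. The working shows movement in both directions. The article does not say that excluded patients' data are deleted or their follow-up stopped. If the data are kept, an analysis of all enrolled patients would show the effect.
- A reader might size the bias by removing a high-risk group. Removing 5% of patients with an assumed 70% event rate gives (0.35 − 0.05 × 0.70) / 0.95 = 33.2%, a drop of 1.8 points. If those patients are truly ineligible, that is simply the rate in the eligible population, and a uniform rule would give the same figure. The bias at issue comes from treating like violators differently.

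It is also true that most criteria are baseline facts with little room for hindsight, and that this is an exploratory descriptive registry. Both points limit the severity.

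**Conclusion.** The concern holds as a defect in a stated rule: removal after enrolment is discretionary, has no criterion, and is not shielded from follow-up knowledge. Outcome-dependent exclusion is possible; the article does not show that it occurred.

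The size cannot be determined, because neither the number of violators nor the degree of selection is given. With an assumed 5% ineligible, the shift in the 35% rate is about 0.6 points under 75% versus 25% selection and about 1.2 points under full selection. The implied half-width is about 2.5 points. The shift is negligible at 1% ineligible and approaches the half-width only at about 10% with full selection. These figures assume the same event rate in ineligible and eligible patients. The point is moderate in weight and should be corrected because the remedy is cheap and the affected rates are the purpose of the registry.

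**What to change.** Replace the discretion with a written rule:

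1. Judge eligibility violations only on data dated at or before inclusion.
2. Give those who judge a listing without follow-up outcomes.
3. Treat every confirmed violator of a given criterion the same way.
4. Keep the data of excluded patients.
5. Report the primary rate in all 1700 enrolled patients alongside the rate in the eligible set.
6. List the exclusions with the reason for each.

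The rule should also say that violations arising after inclusion, such as a missed visit, do not remove a patient from the analysis.

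The cost is a paragraph of text, one baseline-only listing and one additional analysis. The change remains possible now that enrolment is complete, because it concerns only how recorded data are reviewed and reported.

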### Sample Size and Data Collection

Patients eligible according to aforementioned inclusion criteria will be selected at the cardiology consultation level or during cardiology or emergency hospitalization. As much as 250 cardiologists (from both public and liberal sectors) will participate in patient selection. Patient inclusion will occur consecutively until the end of the inclusion period. Suitable patients will be selected and requested to sign an informed consent form, confirming their agreement to participate in the study. A detailed questionnaire will then be administered to eligible patients and clinical, biological, and exploratory data will be collected.

The inclusion began on October 2, 2017 (duration 1 month). A regular follow-up was done, wherein patients must visit the cardiology clinic 1, 3, and 12 months after inclusion into the study. This follow-up is provided by the investigator.

Given the observational nature of the NATURE-HF study, no specific treatment or intervention is planned for the management of HF. Patients should be cared for according to the usual medical procedures.

All data are collected via the DACIMA Clinical Suite web interface [8]. The platform complies with international standards FDA 21 CFR part 11 (Food and Drug Administration 21 Code of Federal Regulations part 11), HIPPA (Health Insurance Portability and Accountability Act), ICH (International Conference on Harmonisation), MedDRA (Medical Dictionary for Regulatory Activities), Health Canada, and Tunisian regulations.

### Statistical Analysis

The DACIMA Clinical Suite platform enables the collection of online data and their extraction in SAS or SPSS format. Statistical analysis will be performed with SAS software (University Edition; SAS Institute). The statistical analysis is exploratory, involving the calculation of 95% CI.

The data will be described for the whole analyzed population. Continuous quantitative variables (eg, age, weight, left ventricular ejection fraction, biological parameters) will be described by the number of patients documented, mean, median, SD, and extreme values. Categorical variables will be described by the number and percentage of each category.

The normality of the continuous quantitative variables will be verified with the Shapiro–Wilk test. If the hypothesis of normality is rejected, then a simple transformation will be made on the variable to normalize it. If this transformation succeeds in normalizing the variable, then the analysis will be performed on the transformed variable. Otherwise nonparametric tests will be used or possibly an analysis on the quartiles or quintiles will be performed.

Statistical tests will be bilateral with a statistically significant threshold of 5%. An analysis of variance will be performed for the quantitative variables (parametric test for the variables that follow a normal distribution, and nonparametric test in other cases) and a chi-square test will be realized for the categorical variables. The Yates correction or Fisher exact test will be used if the validity conditions for the chi-square test are not met (theoretical number <5).

The sample size (both power and sample) is estimated by the SPSS 2008 software (IBM). To estimate the number of patients to be included in this study, a range of 95% CI (5% significance threshold) is set as the primary endpoint. The impact of this criterion is estimated at 35%, based on the US registry OPTIMIZE-HF [9], which found a hospital mortality ranging from 2.2% to 4.1%, a global mortality ranging between 6.5% and 9.1%, and an overall incidence of all events evaluated (rehospitalization or death) ranging from 35.3% to 36.6%.

Considering these data, the number of patients to be included in the study would be 1436. However, by predicting a 5% missing data rate and a 10% loss to follow-up, the sample size to be selected will be 1700 patients.

The intermediate analyses will be carried out after formulating the statistical analysis plan.

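### The rule for comparing quantitative variables depends on normality alone; if SDs differ between very unequal groups, a pooled-variance ANOVA would not hold its 5% level (minor, exploratory comparisons only)

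*Protocol article*

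**What the plan says.** All of this stands in the protocol article, mostly under Statistical Analysis.

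- Assumption check: "The normality of the continuous quantitative variables will be verified with the Shapiro–Wilk test". If normality is rejected, a transformation is tried. If that fails: "Otherwise nonparametric tests will be used or possibly an analysis on the quartiles or quintiles will be performed".
- Test: "An analysis of variance will be performed for the quantitative variables (parametric test for the variables that follow a normal distribution", with a nonparametric test in other cases.
- Level: "Statistical tests will be bilateral with a statistically significant threshold of 5" percent.
- For categorical variables the same paragraph does state when the chi-square test is invalid (small expected counts) and names its replacements, Yates and Fisher.
- Planning figures: 1436 patients before allowance for missing data and loss to follow-up, then "the sample size to be selected will be 1700 patients". The cited US registry gave "a global mortality ranging between 6.5% and 9.1" percent, and the primary event rate is put at 35%.
- Registry Objectives lists as a secondary item the "determination of the predictors of cardiovascular mortality".

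No grouping variable for the ANOVA is named, and no SD is given for any variable. The analysis is described as exploratory.

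**The concern.** Classical ANOVA assumes normality within groups and one common variance. The article's rule addresses only the first. With groups of similar size, unequal variances do little harm. With very unequal groups the pooled variance is almost entirely that of the larger group, so the standard error of the mean difference is wrong if the smaller group is more, or less, dispersed. Neither a large total sample nor a passed normality test removes this.

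At stake is the meaning of the 5% threshold in comparisons that may be used to screen for predictors. Variables more dispersed in the small group would be flagged too often, and variables less dispersed there would be missed. A confidence interval for a mean difference would err in the same direction if it were built on the pooled variance.

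**Working it through.** **Inputs from the article.** Nominal level 5%, two-sided. N = 1436. Death rate 6.5–9.1% (planning source), giving 0.065 × 1436 ≈ 93 versus 1343 and 0.091 × 1436 ≈ 131 versus 1305. For comparison: the Background states that "one-quarter of patients die within 1 year of diagnosis", giving 359 versus 1077, and the 35% primary event rate gives 503 versus 933.

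**Assumed input.** r = SD in the smaller group divided by SD in the larger group. The article gives no value, so a range is shown.

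**Formula** (two groups, no true mean difference, larger-group SD set to 1):

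- pooled variance s² = [(n₁ − 1)r² + (n₂ − 1)] / (n₁ + n₂ − 2)
- variance the test assumes: V_pooled = s²(1/n₁ + 1/n₂)
- true variance: V_true = r²/n₁ + 1/n₂
- true level = 2 × [1 − Φ(t_crit × √(V_pooled / V_true))], with t_crit ≈ 1.96

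**Stated figure first.** With r = 1 the two variances coincide and the formula returns 4.98%, that is, the stated 5%.

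**Worked case, 93 versus 1343, r = 1.25.**

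- s² = (92 × 1.5625 + 1342) / 1434 = 1.036
- V_pooled = 1.036 × (1/93 + 1/1343) = 0.01191
- V_true = 1.5625/93 + 1/1343 = 0.01755
- √(0.01191 / 0.01755) = 0.824, and 1.96 × 0.824 ≈ 1.616
- true level ≈ 10.6%

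**True level of the nominal 5% test:**

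| r (assumed) | 6.5–9.1% split | 25% split | 35% split |
|---|---|---|---|
| 0.67 | 0.6–0.7% | 1.7% | 2.8% |
| 0.8 | 1.7–1.9% | 2.9% | 3.6% |
| 0.9 | 3.2–3.3% | 3.9% | 4.3% |
| 1 | 5.0% | 5.0% | 5.0% |
| 1.1 | 7.0–7.1% | 6.1% | 5.7% |
| 1.25 | 10.2–10.6% | 7.9% | 6.6% |
| 1.5 | 15.7–16.6% | 10.7% | 8.1% |
| 2 | 25.2–27.2% | 15.0% | 10.2% |

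With 1700 patients instead of 1436 the formula gives practically the same levels, because the split matters and not the total. At a 50/50 split it gives 5.0% for every r.

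**Simulation check** (20,000 runs per cell; 110/1590, 136/1564 and 155/1545 of 1700). The pooled test gave 10.2–11.0% at r = 1.25, 15.4–16.9% at 1.5 and 0.6–0.8% at 0.67. Welch's test stayed at 4.7–5.3% for all r from 0.5 to 2.

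**Does the normality check intercept the problem?** The article does not say whether Shapiro–Wilk is applied to the whole variable or within groups. Applied at 5% to the whole variable (136/1564, normal within groups), it was passed in about 91% of samples at r = 1.25, 59% at 1.5 and 0.3% at 2. Among samples that passed, the ANOVA rejected in about 10% at 1.25 and 14% at 1.5. Applied within groups, it is blind to a difference in SD. The nonparametric branch (Mann–Whitney) ran at about 7%, 9% and 13% at r = 1.25, 1.5 and 2.

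**Cost of Welch when variances are equal.** Two simulations of a 0.3 SD difference with 131 versus 1305 gave power of 89.7% against 90.1% and 90.2% against 90.5%, a loss of 0.3–0.4 point.

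**The case against.** The strongest reply is that this is a condensed article which refers to a final statistical analysis plan, not shown, and that the choice between pooled and Welch tests is commonly left to that plan. The article never says that the variance is pooled, and Welch's ANOVA is itself a parametric analysis of variance. In part this stands: the pooled reading is the usual one, but it is an inference. It does not dispose of the point, because the article does not simply stay silent. It fixes a rule with normality as the sole stated condition, while spelling out validity conditions for the chi-square test in the same paragraph. An analysis plan that follows it would inherit the gap.

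Three further objections stand and limit the point. First, died versus survived is inferred from the predictor objective and is not a stated ANOVA grouping. Second, 6.5–9.1% is the planning source's mortality; at the 25% and 35% splits that the article also supports, the distortion is much smaller. Third, the tests are exploratory.

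A reader might infer that these comparisons will in fact run at 10–27%, or below 1%. The documents do not support that. Those rates need SD ratios of 1.25–2, or about 0.7 or less, and the article gives none. For ratios of 0.8–1.2 the level lies between about 1.7% and 9.4%. If Shapiro–Wilk is applied to the whole variable, the ratio-2 cases almost never reach the ANOVA.

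**Conclusion.** The point holds conditionally and is minor. It rests on three assumptions: that the ANOVA is the usual pooled-variance one, that groups as unequal as 93–131 versus 1343–1305 are compared, and that SDs differ between them. The nominal 5% test could then run at about 7% (ratio 1.1), 10–11% (1.25) or 16–17% (1.5), or at about 2% (0.8) or below 1% (0.67). At a 25% split, ratios of 1.25–1.5 give about 8–11%; at a 35% split, about 7–8%. With equal SDs there is no distortion.

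Nor should a reader infer that the registry's main result is at risk. The primary endpoint is an event proportion with a 95% CI, and neither that nor the sample size depends on the ANOVA.

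**What to change.** In the Statistical Analysis section, and in the analysis plan that follows it, state that parametric comparisons of quantitative variables use Welch's ANOVA (the unequal-variance t test for two groups), without a preliminary test of variances, and that any confidence intervals for mean differences are taken from it.

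This is one sentence and a standard software option. It needs no new data and leaves the sample size and the primary analysis as they are. The downside is the power loss of below about 0.5 point when variances are equal.
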